### **Cerebral Hemodynamic Response**

Accompanied by the executive function test, the cortical hemodynamic response in the prefrontal cortex will also be recorded using a multi-channel fNIRS (Octamon fNIRS system, Artinis, Netherland) applying two wavelengths of near-infrared light (785 and 830 nm). The device consists of eight light sources and two detectors secured onto a head cap. The device will be placed over the left and right prefrontal cortex according to the guidelines in the handbook provided by the manufacturer. The data will be analyzed as described [60].

## **Secondary Outcomes**

### **Anthropometry**

Body height, weight, as well as waist and hip circumference will be measured three times. All measurements will follow the Anthropometry Procedures Manual of National Health and Nutrition Examination Survey (NHANES).

### **Social Behavior, Quality of Life, and overall ADHD symptoms**

Conners' Teacher Rating Scale 15-Item (CTRS-15) [61] will be used to measure the social behaviors of participants. It has been widely used to assess problematic behaviors in children with ADHD. Parents will be required to complete a 50-item Child Health Questionnaire-Parent Version (CHQ-PF50) [62] to assess the quality of life of participants. Overall ADHD symptoms will be assessed by the Attention-Deficit/Hyperactivity-symptoms and Normal-

behaviors (SWAN) rating scale [67].

### **Physical Activity**

Children's leisure-time PA will be determined using both an accelerometer (ActiGraph, Shalimar, USA) and a validated and modified version of the Physical Activity Questionnaire for Children (PAQ-C) [63]. Participants will be required to wear an accelerometer on their right hip for seven days to collect objective data of PA levels. The time on and time off of wearing the accelerometer each day will be recorded, and the data will be used to estimate the time spent in moderate-to-vigorous PA (MVPA). The PAQ-C is a 7-day self-report questionnaire designed to assess daily activities from moderate to vigorous range, and the score is in a continuous range from 1 (low active) to 5 (high active).

### **Feelings State**

A one-item Feelings State questionnaire will be administered before and after each intervention session (total 24 sessions). Participants will be asked to respond on an 11-point scale (-5 = very bad to +5 = very good) to the question *How are you feeling right now?* Mean pre- and post-workout scores will be calculated for each session [64].

### **Heart Rate**

Participants will be fitted with Polar H7 heart rate monitors during the training sessions, which will be connected to a central iPad application. The mean heart rate for the entire session and the mean maximum heart rate will be tracked over the study period.

### **Enjoyment and Adherence**

Enjoyment will be assessed by the Physical Activity Enjoyment Scale, which is a valid and reliable tool for evaluating perceived enjoyment [65]. Adherence to the intervention program will be evaluated by attendance frequency and dropout rate.

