Attention-deficit/hyperactivity disorder (ADHD) is a commonly diagnosed developmental disorder, with a 5.3% worldwide prevalence in children and adolescents [18]. The most common symptoms include inattention, impulsivity, impaired inhibition, and hyperactivity [19]. Also, young people with ADHD are often characterized by dysfunction in high level cognitive functions such as executive function [20]. This executive dysfunction may play an important role in the commonly observed behavioral problems in children with ADHD. There are a number of ways to treat ADHD, e.g., medication, psychotherapy, psychoeducation, neuro-feedback, behavior management, etc. Of these treatments, PA and exercise have emerged as effective strategies to manage ADHD given that neither are associated with negative side effects (see recent reviews [21-24]). To summarize, although not always consistently, PA, especially moderate- to high-intensity aerobic exercise, may improve the emotion/mood, behavior, executive function, and some physical measures of children with ADHD. Acute aerobic exercise may have a positive effect on a variety of measures with a large effect size up to 1.26 in children with ADHD [23]. Two studies have reported medium-to-large effects of acute exercise on executive function [25, 26]. Long-term exercise interventions have also been shown to benefit children with ADHD, with improvements in some measures showing a large effect size up to 0.96 [23]. However, these benefits have been mainly described as an improvement of behavioral and emotional problems [22]. Several studies have reported that long-term ‘mixed exercise programs’ may have moderate to significant effects on several aspects of executive function (e.g., inhibition) and attention in children and adolescent with ADHD [27-29], but other studies did not report the same findings [30]. Therefore, so far evidence-based suggestions regarding the optimal exercise for children with ADHD remain somewhat inconsistent [22].

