## **(b) (i) Research plan and methodology**

### **Participants**

A total of 42 children with ADHD will be recruited from local schools. The inclusion criteria are: (1) Chinese children aged 8-13 years; (2) a clinical diagnosis of ADHD by developmental pediatricians or clinical psychologists/psychiatrists; (3) a physician/psychologist's recommendation for participation. The exclusion criteria are: (1) diagnosed with a major neurodevelopmental or psychiatric disorders (e.g., autism spectrum disorder, intellectual disability, etc.); (2) acute/chronic diseases that may affect engagement in physical activity; and (3) a tendency to experience convulsions. Informed consent will be obtained from the school principal, parents, and study participants before the study begins. Human research ethics approval will be sought from the Human Research Ethics Committee of the University.

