### **Sample Size Calculation**

The sample size is calculated using G\*Power 3.1. To elucidate the differences in the executive function tests with a statistical power of 0.9, a conservative effect size of 0.65 based on a previous systematic review with the average effect size calculated regarding the effect of exercise on executive function in children with ADHD [24], a two-tailed alpha level of 0.05, it is determined that 10 participants per group will provide adequate power to detect statistically significant differences. Assuming a 30% loss in the intervention, we will need to approach about 42 eligible participants to achieve the planned sample.

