### **Study Design**

A three-arm school-based randomized controlled trial (RCT) will be conducted to evaluate the effects of two different kinds of 12-week training programs on the executive function of children with ADHD. The design, conduct, and reporting for the RCT adheres to the guidelines of the Consolidated Standards of Reporting trials (<http://www.consort-statement.org/>) [54]. Participants will be randomly assigned to the GameHIIT group, the GameSAE group, or a non-treatment control group using a random number-producing algorithm (with a 1:1:1 allocation ratio within each school). A stratified random sampling procedure will be conducted that considers gender, IQ, and medication status. Raven's Standard Progressive Matrices (SPM) will be used to measure general intelligence. Equal numbers of boys and girls with similar general intelligence will be included in the three groups. Children taking medication will be equally distributed to the three groups. Participants will not be blinded to treatment allocation because of the intervention nature. To avoid contamination between treatment groups, intervention deliverers will be provided with a list of students in the intervention program. Only those on the list can participate in the intervention. During the 12-week intervention period, participants in the control group will maintain their regular PA levels. For ethical reasons, a cross-over study design will be adopted. That is, participants in the control group will receive either GameHIIT intervention or GameSAE intervention according to their preference after a 12-week formal intervention period. Accordingly, participants in the other two groups will have another 12-week follow up. Therefore, it is expected that all participants in the three groups will benefit from the proposed study. The flow diagram of the study design is shown in **Figure 1**.

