## **Intervention Protocols**

In the GameHIIT group, a specially designed game-based training program with HIIT in nature will be delivered to the participants for 12 weeks. A small-sided games (SSGs) approach in rugby will be adopted in this intervention program as it is effective in developing physical and technical capabilities in children, and provides similar physical stimulus, regardless of the experience of the children. Importantly, rugby has been introduced in a large scale to primary and secondary schools in Hong Kong. There will be two training sessions each week. In each training session, there will be four sets of training programs separated by 3 minutes of passive recovery in accordance with a previous study. Each set of activities will last for around 5 minutes; therefore, the total duration of each training session will be approximately 30 minutes. A brief description of the proposed training program is given in **Table 1**. A small group size (4-6 children per group) will be adopted to facilitate individual supervision and adaption of the exercise program. Also, certain social, cognitive and coordinative elements will be included which may play an important role in liking the neuropsychological concept of executive function. All the training programs will be organized for participants after school hours. A qualified rugby coach will be hired to implement the rugby training program. To encourage maintenance of an appropriate level of exercise intensity, participants will be fitted with heart rate monitors (Polar H7), which will be connected to a central iPad application (Polar Team). The coach will be able to view real-time HR data during training. If necessary, we will adjust the exercise intensity to ensure that HR can reach the target HR zone. Adherence to the designed GameHIIT protocol will be recorded by the coach in each training session.

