In the GameSAE group, participants will attend a tailor-made game-based exercise training program designed by one of our group members. Similar to GameHIIT, the intervention will comprise 12 weeks of structured aerobic exercise sessions, lasting one hour on average in each session and up to twice per week. Six to eight stations of multidimensional exercises will be set up for each session. Adopting the train-the-trainer (TTT) model, training will be provided by front-line healthcare providers who are mainly social workers. Children will be instructed to finish the exercises in all stations one after another in a predetermined order. The exercise program has 3 stages and each of the stage last around four weeks. In the first stage, the aim is to build trust to their coaches, and paired group activities are included. In the second stage, the exercise intensity will be increased to promote cardiopulmonary endurance and muscular strength. In the final stage, the exercise intensity for each session will be higher than that of the previous stages and there will be large group activities as well. To record the progress of the training classes and provide feedback to the front-line healthcare providers, a professional coach and research assistant will take part in the training once every two weeks.

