## **Outcomes Measurements**

Before (T0) and after (T1) the 12-week intervention period, as well as another 12-week follow up (T2), several different indicators will be recorded, including executive function, cerebral hemodynamic response, weekly PA levels, physical fitness, feeling state, and enjoyment and adherence to the intervention. All assessments will be conducted by trained research staff blinded to group allocation. To ensure the accuracy and consistency of the measurements, a measurement training session and protocol manual, including specific instructions for

conducting all assessments, will be provided to the research staff. A senior researcher will be present during all the testing sessions. All physical assessments will be conducted in a sensitive manner (e.g., weight/waist circumference will be measured in a private setting), and the cognitive function tests and questionnaires will be completed under exam-like conditions. Also, participants will be instructed to follow similar diets on the main trial days. Only distilled water will be allowed before the tests in the main trials.

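### Harms are an outcome in no arm and no reason for absence or withdrawal is recorded, so a child who stops through injury counts only as poor adherence

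*Protocol*

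**What the plan says.** The Protocol, Outcomes Measurements, lists what is recorded at T0, T1 and T2: "executive function, cerebral hemodynamic response, weekly PA levels, physical fitness, feeling state, and enjoyment and adherence to the intervention". The sections that follow define the individual measures: executive function, prefrontal haemodynamics, anthropometry, behaviour, quality of life and ADHD symptoms, physical activity, feelings state, heart rate, enjoyment and adherence, and fitness. None is an injury or adverse-event item.

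Withdrawal is treated in two places. Under Enjoyment and Adherence: "Adherence to the intervention program will be evaluated by attendance frequency and dropout rate". Under Sample Size Calculation: "Assuming a 30% loss in the intervention, we will need to approach about 42 eligible participants to achieve the planned sample". Neither provides for recording a cause. Statistical analyses then uses attendance as a covariate for the primary and secondary outcomes.

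The protocol does recognise that exercise carries some risk. The exclusion criteria under Participants include "2) acute/chronic diseases that may affect engagement in physical activity; and (3) a tendency to experience convulsions". The Background, on the other hand, says of physical activity and exercise that "neither are associated with negative side effects".

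Two staff records are described under Intervention Protocols. For GameHIIT: "Adherence to the designed GameHIIT protocol will be recorded by the coach in each training session". For GameSAE, to record class progress and give feedback to the providers, "a professional coach and research assistant will take part in the training once every two weeks".

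**The concern.** An analysis plan can only analyse what was collected. If nobody is asked to note an injury, or why a child left, a later document cannot recover it. This is therefore a protocol matter and not one to leave to the SAP.

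Three things are at stake. First, the trial would have nothing to report on harms from 12 weeks of high-intensity games in children. The Background says that earlier exercise research in ADHD was generally of low to moderate intensity, and it knows of only one HIIT study in this population: 28 boys over three weeks. Second, the dropout rate is meant to show how well the programme is adhered to, but it would not separate children who lost interest from children who were hurt or unwell. Third, absence caused by injury would enter the ANCOVA through the attendance covariate without being identified as such.

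**Working it through.** **1. Does any described measure capture an event or a cause?**
- Feelings State: one mood rating at the start and end of each session. It records neither an event nor a cause.
- Heart Rate: session mean and maximum, an intensity measure.
- Attendance and dropout: counts.
- Behaviour, quality-of-life and symptom scales: described as ratings of those constructs, not as a record of events.
- Executive function, haemodynamics, anthropometry, physical activity, fitness, enjoyment: none concerns harms.

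A child who has left the programme no longer supplies the session measures, and controls have no sessions in weeks 1 to 12. The described measures do not fill the gap.

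**2. The plan's own figures**
- Sessions: 12 weeks × 2 per week = 24, which matches the total under Feelings State.
- Sample size: 3 × 10 = 30 completers; 30 / (1 − 0.30) = 42.9. The stated figure of about 42 is reproduced to within one child.
- Arm size: allocation is "with a 1:1:1 allocation ratio within each school", so 42 / 3 = 14 per arm.

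**3. How many children the missing cause could concern**
- 0.30 × 42 = 12.6, about 13 children; per arm 0.30 × 14 = 4.2, about 4.
- This is the planning allowance, not a forecast. The number who would leave for health reasons is unknown, and the plan gives no means of finding out.

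**4. What complete harm recording could show**
- With zero events in n children, the one-sided 95% upper bound p solves (1 − p)^n = 0.05, so p = 1 − 0.05^(1/n).
- n = 14 (one arm as randomised): 1 − 0.05^(1/14) = 0.193.
- n = 10 (the planned completers in one arm): 1 − 0.05^(1/10) = 0.259.
- n = 28 (both exercise arms together): 1 − 0.05^(1/28) = 0.101.
- Conversely, if the true risk per child were 10% (an assumption), the chance of at least one event among 14 would be 1 − 0.9^14 = 0.77; at 20% it would be 1 − 0.8^14 = 0.96.

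The data could reveal a common problem but could not establish safety or support a formal comparison between arms.

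**5. Secondary: which existing record could carry harms**
- GameHIIT: the coach records every session, 24 of 24.
- GameSAE: a coach and research assistant join every two weeks, 12 / 2 = 6 visits. That is 6/24 = 25% at the maximum of two sessions a week, or 6/12 = 50% if the class met once a week (an assumption; the protocol gives only an upper limit).

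Harms collected only through these two records would be looked for unequally in the two exercise arms.

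**The case against.** **Much is already recorded at sessions.** Feelings State, heart rate and attendance are not limited to GameHIIT. A reader might infer from the fortnightly visits that GameSAE has session records for only a quarter of its sessions, and that this is why the arms cannot be compared for safety. The documents do not support that. Only the visiting coach's and research assistant's progress record is fortnightly, and nothing says that the providers who lead the classes keep no record. The two staff records cover adherence and class progress, not harms. Safety cannot be compared because harms are collected in no arm.

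**No biased harm count is planned.** A reader might go on to predict that GameHIIT will show several times as many events at equal true risk. If the risk per session were r in both arms and events were seen only when these staff attend, the ratio would be 24r / 6r = 4, however many sessions GameSAE runs. Figures such as 18/6 = 3 or 12/6 = 2 describe how far GameSAE events would be under-recorded and are not ratios between arms. The premise is also arbitrary, since GameHIIT sessions last about 30 minutes and GameSAE sessions about an hour, and the protocol does not plan to reconstruct harms from these notes. No multiple should be quoted as a consequence of the plan.

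**The Background remark is not a hypothesis.** This is right. It is a literature statement supporting exercise as a treatment option, and the hypotheses concern executive function. The remark explains why harms may have been overlooked; the trial does not claim to test it.

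**Safeguards and reporting standards exist.** Eligibility requires a professional's recommendation, ethics approval will be sought, groups are small and supervised, heart rate is watched in real time, and the protocol commits to CONSORT and refers to a flow diagram that is not shown. These reduce risk or govern reporting. In the text at hand, none provides for collecting events or reasons for withdrawal.

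**Small numbers.** With 14 per arm, harm data can only be descriptive. That is granted, and it limits what the fix should promise, but descriptive data are still better than none.

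**Conclusion.** The point holds in this form: no arm has a harms outcome, no cause of absence or withdrawal is recorded, and every dropout is read as an adherence result. Followed exactly, the plan yields no harm data and a dropout rate of mixed meaning. At the planned allowance that rate would cover about 13 of 42 children, about 4 per arm. Unequal staff observation (24 of 24 sessions in GameHIIT against about 6 of up to 24 in GameSAE) is secondary. It matters only for choosing where harms are to be recorded.

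The conclusion rests on the protocol text alone and assumes that no separate safety-reporting procedure exists that is not shown. It does not imply that either programme is unsafe, and it does not touch the sample size or the primary analysis. It is a low-cost improvement that should be made before sessions begin, because the information cannot be reliably recovered afterwards.

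**What to change.** 1. Add harms (injury, convulsion, other adverse event) as a descriptive secondary outcome.
2. Add one line to a log completed at every session by whoever leads it: any event, and the reason for each absence or withdrawal. Use the same log in GameHIIT, in GameSAE and for controls who train after week 12. Do not rely on the GameHIIT adherence record and the fortnightly GameSAE visit alone.
3. Ask all three arms the same event question at T1 and T2. Controls have no session log in weeks 1 to 12, so any three-arm description for that period should use this question, with the log used for the two exercise arms. Placing the question beside the questionnaire that parents already complete would help keep the assessors blinded.
4. Report dropout split into health-related and other causes, and events by arm, descriptively and with upper confidence bounds. Keep the period after week 12 separate, because controls may then be training.

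The cost is a few minutes per session for session leaders and one question at visits already planned. No extra staff are needed, and neither the sample size nor any treatment rule changes.

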### **Physical Fitness**

Physical fitness (cardiovascular fitness, muscular strength and speed-agility) will be assessed using the ALPHA fitness test battery [66]. Briefly, cardiovascular fitness will be assessed by the 20 m shuttle run test; muscular strength will be assessed by the handgrip strength test and standing long jump test; and speed-agility will be assessed by the 4 × 10 m shuttle run test [66].

### **Statistical analyses**

Statistical analyses of the primary and secondary outcomes will be conducted with the IBM SPSS Statistic for Windows, Version 20.0 (2010 SPSS Inc., IBM Company Armonk, NY). Intervention effects for the primary and secondary outcomes will be examined by two-way (trial × time) analysis covariance (ANCOVA), including group as a fixed factor, pre-post intervention difference (change) as the dependent variable, and age, attendance, sports skill, and ADHD symptoms as covariates. Effect sizes (ES) will be presented as partial eta squared values ( $\eta^2$ ). Pairwise comparison will be performed (post-hoc) with Bonferroni correction, with ES presented as Cohen's *d*. Correlational analysis will also be conducted to evaluate the relationship between the changes in executive function and the fNIRS measures. All data will be presented as mean ± SD, and significance will be set as  $p < 0.05$  for all data analysis.

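### The three-arm change-score ANCOVA, set for secondary outcomes without exception, cannot be applied to session heart rate, per-session Feelings State or attendance-based adherence

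*Protocol*

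**What the plan says.** The rule is in the Protocol, Statistical analyses: "Intervention effects for the primary and secondary outcomes will be examined by" a two-way ANCOVA (trial by time). Group is the fixed factor, with "pre-post intervention difference (change) as the dependent variable, and age, attendance, sports skill, and ADHD symptoms as covariates". No outcome is exempted.

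The outcomes in question all stand under Secondary Outcomes:

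- Feelings State: "A one-item Feelings State questionnaire will be administered before and after each intervention session (total 24 sessions").
- Heart Rate: "Participants will be fitted with Polar H7 heart rate monitors during the training sessions".
- Enjoyment and Adherence: "Adherence to the intervention program will be evaluated by attendance frequency and dropout rate".

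Three other places bear on them:

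- Study Design gives three arms. One receives no treatment and keeps to its usual activity for the 12 weeks. Its children are offered a programme of their own choice only afterwards.
- Outcomes Measurements includes "feeling state, and enjoyment and adherence to the intervention" among the indicators recorded at T0, T1 and T2.
- Intervention Protocols sets two GameHIIT sessions a week, and describes GameSAE sessions as "lasting one hour on average in each session and up to twice per week".

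**The concern.** A pre-post change model with three groups needs a before value and an after value for each child in each arm. Outcomes that exist only while a child is training meet neither condition. The plan nevertheless puts them under the same rule as executive function and fitness, and adds attendance as a covariate even where attendance is the outcome.

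Run as written, the rule gives no estimate or an empty one for these outcomes. The protocol's background argues for game-based exercise partly on enjoyment and likely long-term adherence, and heart rate is the check that the intended intensity was reached. A reader of the results would want these figures for the two programmes side by side. An analyst who met the problem after the data were in would have to improvise the analysis.

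**Working it through.** The plan gives no figure to reproduce here. The check compares what the model needs with what the protocol measures, and then looks at the algebra of the attendance covariate.

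**Step 1. What the model needs and what exists from T0 to T1**

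| Outcome | Value in controls | Value before the programme | Three-arm pre-post change |
|---|---|---|---|
| Session heart rate | None, no sessions | None | Does not exist |
| Feelings State | None, no sessions | Only before each session | Does not exist; the within-session change is a different quantity |
| Attendance frequency | None, or zero by design | None | Does not exist |
| Dropout rate | Study dropout can be counted | Not applicable | A proportion per arm, not a child-level change |
| Enjoyment | Not settled by the text | Not settled by the text | Depends on who is asked, and when |

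Sessions that controls attend after T1 cannot fill the gap, because they fall outside the randomised comparison and are in a programme chosen by preference. The first three rows also show the conflict with Outcomes Measurements: a per-session score and an attendance record are not T0, T1 and T2 measurements.

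**Step 2. Attendance adjusted for attendance**

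Suppose the missing baseline is set to zero, so that the change equals attendance A. The model is

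A = b0 + b1·GameHIIT + b2·GameSAE + c·A + (age, skill, symptoms) + error.

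Least squares is solved exactly by c = 1 with every other coefficient 0. A numerical check on illustrative data (10 children per arm) gave an attendance coefficient of 1, group coefficients of 0 and a residual sum of squares of about 2 × 10⁻²⁷. No arm difference in attendance can be tested. If the baseline is not set to zero, there is no response variable at all.

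**Step 3. Attendance in the remaining three-arm models**

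- *Left blank for controls.* Listwise deletion removes the control arm. In the illustration, 20 of 30 children and 2 of 3 arms remain, so 1 of 3 pairwise contrasts survives. The design matrix has rank 6 for 7 columns.
- *Coded zero for controls.* Assume each child in the exercise arms attends 80% of 24 sessions, independently. Their mean is 0.8 × 24 = 19.2 and their variance is 24 × 0.8 × 0.2 = 3.84. With two thirds of children in the exercise arms:
  - between-status variance = (2/3)(1/3)(19.2²) = 81.92
  - within-status variance = (2/3)(3.84) = 2.56
  - R² of exercise-versus-control status on attendance = 81.92 / (81.92 + 2.56) = 0.97

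  The simulated 30 children gave 0.98. The covariate then nearly duplicates the comparison of interest. A wider spread of attendance would lower this figure. It would not change the fact that attendance arises after randomisation and is fixed at zero in one arm.

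**Step 4. Number of sessions**

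Two a week for 12 weeks is 2 × 12 = 24, which matches the Feelings State total and the GameHIIT schedule. For GameSAE the wording makes 24 a maximum. The denominator for attendance in that arm is therefore not fixed.

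**The case against.** The strongest case for leaving the text alone is that the rule concerns intervention effects, which a measure with no counterpart in controls cannot have. On that view heart rate, Feelings State and adherence are delivery measures with their own summaries: mean scores for each session, heart rate tracked over the study, and attendance and dropout. No analyst would regress attendance on itself, and handling outcome by outcome can be left to a SAP.

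Part of this stands. The summaries are reasonable as description, and a formal model for Feelings State is optional. But the protocol files these measures under Secondary Outcomes and then fixes one model for secondary outcomes without exception. That is a stated rule that fails, not a detail left open.

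Several stronger readings are tempting, but the protocol does not support them:

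- *Enjoyment also lacks a control value.* A reader might infer this, but the protocol does not tie the scale to sessions or to the exercise arms, and it lists enjoyment at T0, T1 and T2. The phrase in Outcomes Measurements can be read either way.
- *Attendance counts differ twofold by schedule.* This needs GameSAE to offer one session a week (12 against 24) and attendance to be a raw count. The protocol states neither.
- *The zero arm effect covers all of adherence.* It covers attendance frequency. Dropout is a separate measure and can be counted in controls.
- *The secondary hypothesis is at risk.* That hypothesis is that GameHIIT may add benefit over GameSAE, in a paragraph about executive function and its mechanism. It is not about acceptability.

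**Conclusion.** The point holds for three secondary outcomes: session heart rate, per-session Feelings State and attendance-based adherence. None has a control value in the randomised period, none has the pre-post change that the model requires, and the attendance adjustment is circular for adherence. The T0/T1/T2 list contradicts the outcome sections for feeling state and adherence. Enjoyment is ambiguous and needs clarifying; it is not a demonstrated failure.

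The mismatch itself does not touch the primary outcome. The attendance covariate does, because it is undefined or zero in controls in every three-arm model.

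The algebra in step 2 rests on no assumed figure once the baseline is set to zero. The R² of 0.97 to 0.98 rests on an assumed 80% attendance and is illustrative. A two-arm comparison of heart rate assumes that monitors are worn in both programmes. The Heart Rate section names no arm, while Intervention Protocols describes the monitors only for GameHIIT.

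This should be corrected before analysis.

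**What to change.** In Statistical analyses:

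- Restrict the three-arm ANCOVA to outcomes measured at T0 and T1 in all arms, and remove attendance from its covariates.
- Compare heart rate and Feelings State (post minus pre within session) between GameHIIT and GameSAE only, or summarise them by arm, without attendance as a covariate.
- Report adherence by arm as sessions attended divided by sessions offered, plus dropout.

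In Outcomes Measurements and the outcome sections:

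- Correct the timing list for feeling state and adherence.
- State when and in which arms enjoyment is measured. If it is taken in all arms at T0 and T1, keep it in the three-arm analysis; otherwise compare it between the exercise arms only. Do not delete a baseline enjoyment measure on an assumption.
- Reconcile Intervention Protocols and Feelings State on the number of sessions offered in each programme.

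The cost is a few sentences and no new data. The downside is that these outcomes support only a two-arm or descriptive comparison.
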